#### Permitted Care During the Trial

Certain medications could impact motor recovery, particularly GABAergic treatments, which were closely monitored. Patients already on a long-term prescription (over 1 month) of sleeping or anxiolytic treatment might continue this treatment. Discontinuing these patients’ medications had more drawbacks than benefits. Zolpidem and zopiclone, commonly prescribed to patients with poststroke sleep disorders, were permitted during this trial.

Considering the prevalence of poststroke depression and its influence on functional recovery, specific antidepressants are authorized. Antidepressants in the serotonin reuptake inhibitor class were permitted. These medications could potentially facilitate motor recovery irrespective of their antidepressant properties [23]. However, randomization aimed to evenly distribute these treatments across all groups, which minimized the risk of bias.

For secondary stroke prevention, patients were administered treatment according to current recommendations (antiplatelet agents, antihypertensive agents, and cholesterol-lowering agents). Effective-dose anticoagulants (heparin and anti–vitamin-K) were grounds for noninclusion due to the risk of muscle hematoma during injections. However, if necessary, during the protocol postinjection, effective-dose anticoagulants were prescribed without necessitating withdrawal from the study.

It is important to note that all patients received standardized functional neurorehabilitation for 2 hours daily, which included physiotherapy and occupational therapy sessions in line with current practices.

#### Prohibited Care During the Trial

Anxiolytics and other benzodiazepines were prohibited, except zolpidem or zopiclone, which may have been prescribed for the duration of the protocol. Similarly, neuroleptics and tricyclic antidepressants were contraindicated due to their deleterious effects on recovery. Effective-dose anticoagulants at the time of inclusion were a criterion for noninclusion.

### Outcomes

#### Primary Outcome: FMA

The primary end point is the progression of the FMA score from allocation (V0) to the visit three months after allocation (V2) [24].

This is a tool for assessing the motor function of participants with hemiplegia after a stroke. It is also recommended by the European Stroke Organization as a poststroke evaluation outcome [25]. Sensitivity to change is moderate for the overall scale and better for the upper limb subscale after a recovery period. This scale has excellent test-retest reliability and interrater reliability [26]. The floor effect and the ceiling effect are good [27]. This scale is widely used in current practice in France and the study investigators are accustomed to performing it.

#### Secondary outcomes

##### Fugl-Meyer Motor Assessment

Subscores of FMA, specifically FMA-UE and FMA-lower extremity (FMA-LE), from allocation (V0) to the visit 3 months after allocation (V2) are secondary end points.

The progression of the FMA score from allocation (V0) to the visit 1 month after allocation (V1) is a secondary end point.

##### Tardieu Scale

Spasticity is assessed using the Tardieu Scale [28]. This scale is of better metrological quality than the Ashworth scale usually used in this type of study [29]. It allows the analysis of the resistance to stretching at several different speeds. Two speeds are used: XV1 is the slowest possible stretching speed and XV3 is the fastest possible stretching speed. Two results are noted: first, the Tardieu angle, which is the difference between the angle of passive joint amplitude obtained at XV1 and the angle of the first resistance to stretching at XV3, and second, the Tardieu intensity score of the resistance to stretching measured by an ordinal score from 0 to 4.

The end point was the progression from the allocation to 1 month later (V0 to V1) and from the allocation to 3 months later (V0 to V2), focusing on muscle groups such as the triceps surae (knee flexed and extended), carpal flexors, and elbow flexors. This score can be applied to muscles that have not been injected, but given the global action of baclofen, measurement of all these muscle groups was essential.

##### Modified Ashworth Scale

The MAS evaluates muscle tone of the same muscles evaluated with the Tardieu Scale. However, it primarily assesses the intensity of resistance to stretching without considering stretching speed [30]. It is therefore much less precise than the Tardieu Scale in terms of the increase in the myotatic reflex, but it allows a very global consideration of the modifications of the intrinsic biomechanical properties of the muscle fibers and the dystonia of the muscles examined. The end point was the progression from the allocation to 1 month later (V0 to V1) and from the allocation to 3 months later (V0 to V2) on the same muscle groups.

##### RMA

The RMA, validated in individuals with vascular hemiplegia [31], appraises motor performance across various functional aspects, including balance, walking, trunk and lower limb motor skills, and upper limb activities. The end point was the progression from the allocation to 3 months later (V0 to V2).

##### Rankin Score

The Rankin score is a widely accepted scale for the global assessment of poststroke disability [32]. It features 6 degrees and is an evaluation tool recommended by the Haute Autorité de Santé. The end point was the progression from the allocation to 3 months later (V0 to V2).

##### Barthel Score

This scale measures autonomy in the activities of daily living and has been validated in individuals with vascular hemiplegia [33]. It comprised 10 items and demonstrated excellent reproducibility. The end point was the progression from the allocation to 3 months later (V0 to V2).

##### Pain via VAS

Changes in pain were evaluated using a VAS from the allocation to 1 month later (V0 to V1) and from the allocation to 3 months later (V0 to V2).

##### Quality of Life Measurement Via the RNLI Questionnaire

The RNLI questionnaire assessed the quality of life specifically for individuals with vascular hemiplegia [34] and was measured from the allocation to 3 months later (V0 to V2).

##### Reaction Time Measurement

Sound and visual reaction time assessments via laptop aimed to quantify the overall impact of spasticity treatments on cognitive functions. The change in measurements was assessed from the allocation to 1 month later (V0 to V1) and from the allocation to 3 months later (V0 to V2).

##### Treatment Satisfaction Via VAS

Patient satisfaction with spasticity treatment was compared using a VAS at both postallocation visits (V1 and V2).

##### Safety

Adverse events (AE) were systematically monitored at the allocation visit (V0), both postallocation visits (V1 and V2), and the close-out visit (V3). Monitoring covered sedation, somnolence, fatigue, muscular weakness, swallowing difficulties, epileptic seizures, liver function, and blood count.

### Sample Size

The study includes three arms as follows: (1) the “toxin” group, which receives an injection of botulinum toxin and placebo oral baclofen; (2) the “baclofen” group, which receives oral baclofen and an injection of placebo botulinum toxin; and (3) the “placebo” group, which receives placebo oral baclofen and an injection of placebo botulinum toxin. All groups receive standard neurorehabilitation care.

This study is a randomized parallel 2-2-1 type design, which corresponds to the “toxin,” “baclofen,” and “placebo” groups, respectively. The main objective, which is to demonstrate the superiority of “toxin” over “baclofen” on motor function, corresponds to a 2-2 comparison. The secondary objective, which is to demonstrate the noninferiority of “toxin” to “placebo” on motor function, corresponds to a 2-1 comparison. The “placebo” arm is limited due to ethical considerations.

The sample size for the “toxin” and “baclofen” arms was calculated with the 2-sided test at a 5% significance level. This analysis compared the superiority of the toxin over baclofen indicated by the FMA gain, between the allocation visit (V0) and the second postallocation visit (V2). The expected variation in FMA was estimated at 30 points between V0 and V2. [35]. For an 85% power and an FMA difference of 12 points between the “toxin” and “baclofen” groups, 120 patients per group were initially required, accounting for missing data and protocol deviations. This 12-point difference was based on the minimal clinically important difference of FMA, which was approximately 6 points for both the upper [36] and lower extremities [37]. Doubling the minimal clinically important difference for a total FMA score ensured a clinically significant change.

To demonstrate equivalence between the “toxin” and “placebo” groups, a 12-point unilateral zone of equivalence was defined. With an SD of 30 points, 60 patients in the “placebo” arm yielded a power of approximately 80% (77.6%), accounting for 10% missing data.

The original target was 300 patients, but by September 30, 2018, only 140 had been included. Given the time and funding constraints, an amendment increased the target FMA difference to 13 points between V0 and V2. This adjustment, while slightly higher, remains within a clinically meaningful range and is achievable under the study’s operational constraints. Accordingly, 85 participants were required in both the “toxin” and “baclofen” groups, factoring in a 10% data loss. The “placebo” group was reduced to 44 patients to maintain the 2-2-1 randomization ratio. A total of 214 patients were therefore needed for trial inclusion.

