### Statistical Methods

#### Statistical Methods for Primary and Secondary Outcomes

The baseline characteristics of the participants are described for the 3 treatment groups and the pairwise standardized differences are used to compare the distribution of baseline covariates between treatment groups.

The variation in the Fugl-Meyer score between the “toxin” and “baclofen” groups is compared using linear regression models. First, the model contains the treatment group as the explanatory variable and the Fugl-Meyer delta score as the response variable. The adjusted model then incorporates the patient’s age, the center, and any associated treatment as explanatory variables, in addition to treatment. The associated treatment is represented by a binary variable indicating the use of at least 1 serotonin reuptake-inhibiting antidepressant (yes or no) or at least 1 benzodiazepine (yes or no). This list is validated during the descriptive analysis of concomitant treatment.

The primary objective tests the superiority of the “toxin” versus “baclofen” in motor recovery at 3 months using 2-sided tests at a 5% α level. The secondary objective aims to demonstrate the clinical equivalence of the “toxin” versus the “placebo” in motor recovery after 3 months, using a 1-sided noninferiority test at a 5% α level and a margin of 13 FMA points to assess noninferiority.

To assess the efficacy of these treatments on spastic symptoms (MAS, Tardieu angle, and Tardieu Scale), 2-tailed *t* tests at a significance level of 5% are conducted for pairwise comparisons. The first analysis is carried out on all muscle groups, and a second analysis is carried out on the muscle groups that have been injected.

For the FMA at 1 month and the variation score between allocation and the second postallocation visit which consists of the RMA the Barthel Index, the Rankin score, the reaction time, satisfaction, pain, and the RNLI, the analyses will be descriptive using the usual statistical measures in each group with a 95% CI.

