## Results

The first participant was included on April 20, 2015, and the last on July 9, 2020. A total of 184 poststroke participants were included, with 179 randomized across 18 centers. Regarding the ancillary study, 28 poststroke participants agreed to participate, and 20 healthy participants were included between March 10, 2021, and May 27, 2021.

In December 2024, all data are currently kept by the data manager. The data quality review is underway. It should be completed in January 2025. After this date, the database will be frozen and statistical analyses can begin. The blind will be lifted after statistical analyses.

In December 2024, investigators had no data, no conclusions could be drawn, and no result trends could be identified.

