### Strengths and Limitations

A major strength of this study is its design, which integrates both placebo and active comparator groups to rigorously assess the effects of botulinum toxin and baclofen on motor recovery. The inclusion of a placebo group—despite ethical and logistical challenges—is crucial for disentangling treatment effects from natural recovery processes. Additionally, the ancillary imaging study offers a unique opportunity to explore the central effects of these treatments on brain plasticity.

However, the study has limitations. While the adjusted sample size is sufficient to detect clinically meaningful differences, it may reduce sensitivity to smaller effects on motor recovery outcomes. Furthermore, the follow-up period of 4 months, though valuable for assessing short-term outcomes, does not capture long-term effects or delayed AEs. Extending follow-up durations in future studies could provide more comprehensive insights into sustained efficacy and safety profiles. Nevertheless, the 3-month follow-up in this study offers valuable early insights into the immediate posttreatment phase, which is a critical period for poststroke motor recovery.

Practical or operational issues arose during the course of the study, reflecting the complexity of its implementation. Securing funding from the PHRC in 2010 marked the first step, but the subsequent year-long process to obtain administrative approvals and transfer funds delayed the study’s initiation. Ensuring blindness between baclofen tablets and their placebo required encapsulating baclofen tablets after a request to affix the manufacturer’s logo was denied. This additional step, involving patient safety measures like verifying expiry dates, added another 2 years. Consequently, the first patient inclusion occurred in 2015. The inclusion rate was slower than anticipated, necessitating a protocol extension and recalculating the required sample size to maintain sufficient statistical power. The COVID-19 pandemic further disrupted the recruitment process in 2020, causing additional delays. Despite these challenges, the study progressed without major technical or procedural issues. Importantly, the question of whether early spasticity treatment affects motor recovery remains unresolved, underscoring the relevance of this research.

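### The amended 85 per active arm does not follow from the stated inputs: it gives about 76% power for 13 points, and the 179 randomized give about 69–74%, yet the article calls the size sufficient

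*Protocol article*

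**What the plan says.** The Sample Size section of the protocol article says that the size of the active arms "was calculated with the 2-sided test at a 5% significance level". It puts the expected variation in FMA change at 30 points and continues: "For an 85% power and an FMA difference of 12 points between the “toxin” and “baclofen” groups, 120 patients per group were initially required", a figure that is said to allow for missing data and deviations. For the toxin–placebo comparison it takes an SD of 30 and a 12-point zone, and reports that "60 patients in the “placebo” arm yielded a power of approximately 80% (77.6%), accounting for 10% missing data".

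After slow recruitment, an amendment raised the target difference to 13 points: "Accordingly, 85 participants were required in both the “toxin” and “baclofen” groups, factoring in a 10% data loss". The placebo arm was cut to 44, for a total of 214. The text announces no change in power, SD or sidedness, and it does not restate noninferiority power for 44 placebo patients.

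The Statistical Methods section keeps the primary test two-sided, testing superiority "in motor recovery at 3 months using 2-sided tests at a 5% α level", and sets the noninferiority margin at 13 points with a one-sided 5% test. The Results section reports: "A total of 184 poststroke participants were included, with 179 randomized across 18 centers". Under Strengths and Limitations, the article opens a sentence with "While the adjusted sample size is sufficient to detect clinically meaningful differences" and then concedes lower sensitivity to smaller effects. The same section says that the size was recalculated to keep power adequate.

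**The concern.** The amendment presents 85 as the consequence of moving from 12 to 13 points. Required size scales with the inverse square of the difference, so that move alone cuts it by 15%, since (12/13)² = 0.852. The stated size falls by 29%, from 120 to 85. Something else must have changed, and the article does not say what.

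The figure supports the claim that the trial can answer its primary question. If power is well below the planned level, a nonsignificant toxin–baclofen result, or a failed noninferiority test against placebo, is more likely to be taken as evidence about the treatments when it may reflect trial size. The article intends the trial to inform recommendations on first treatment of early spasticity.

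**Working it through.** **Inputs.** From Sample Size: two-sided α 0.05, power 85%, SD 30 (called variation for the active arms and SD for the placebo comparison), difference 12 then 13, loss 10%, allocation 2:2:1. From Statistical Methods: two-sided primary test, noninferiority margin 13, one-sided 5%. From Results: 179 randomized. The split by arm is not given, so 2:2:1 is assumed (71.6 / 71.6 / 35.8).

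**Formulas** (normal approximation)
- Evaluable n per arm = 2(z₁₋α/₂ + z_power)²(SD/Δ)²; randomized n = evaluable n / 0.9.
- Power = Φ(Δ/SE − 1.96), with SE = SD·√(2/n).
- Noninferiority power at a true difference of zero = Φ(margin/SE − 1.645), with SE = SD·√(1/n_placebo + 1/n_toxin).

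**1. Original figures, to confirm the inputs**
- Primary: 2(1.960 + 1.036)²(30/12)² = 112.2, so 113 evaluable. The stated 120 leaves room for about 6% loss; at 10% loss (108 evaluable) power is 83.6%.
- Noninferiority: 54 v 108 evaluable, SE = 30√(1/54 + 1/108) = 5.0, Φ(12/5 − 1.645) = 77.5%, against 77.6% stated.

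Both fit, so SD 30 is the planning value.

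**2. Amended size, difference 13**

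| Conditions | Evaluable per arm | Randomized per arm, 10% loss |
|---|---|---|
| Two-sided 5%, 85% power | 95.6 → 96 | 107 |
| Two-sided 5%, 80% power | 83.6 → 84 | 94 |
| Stated in the article | – | 85 |

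**3. What could produce 85**
- A one-sided 5% test at 85% power: 2(1.645 + 1.036)²(30/13)² = 76.6, and 76.6/0.9 = 85.1. This contradicts the two-sided test in both sections.
- A two-sided test at 80% power with no loss added: 84. This contradicts the stated 10% loss.
- A smaller SD: 26.8 for 85% power, or 28.7 for 80%. Neither is stated.

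**4. Power for the primary comparison (SD 30, two-sided 5%)**

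| Scenario | Evaluable per arm | 13 points | 12 points |
|---|---|---|---|
| 85 randomized, 10% loss | 76.5 | 76.4% | 69.6% |
| 179 randomized, no loss | 71.6 | 73.7% | 66.8% |
| 179 randomized, 10% loss | 64.4 | 69.1% | 62.2% |

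For the first row, SE = 30√(2/76.5) = 4.85, 13/4.85 = 2.68, and Φ(2.68 − 1.96) = 0.764. Noncentral-t values for 13 points are 75.9%, 73.1% and 68.5%.

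Detectable difference at 64.4 per arm: 30 × 2.996 × √(2/64.4) = 15.8 points at 85% power; with 2.802 in place of 2.996, 14.8 points at 80%.

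**5. Noninferiority power, 10% loss**

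| Scenario | Evaluable, placebo v toxin | Margin 13 | Margin 12 |
|---|---|---|---|
| Amended, 44 v 85 | 39.6 v 76.5 | 71.5% | 65.5% |
| 179 randomized | 32.2 v 64.4 | 64.2% | 58.3% |

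**The case against.** The amendment paragraph names no power, SD or sidedness, and amendment details are referred to an appendix that is not shown, so carrying over 85% is an inference. That is fair. If the amendment moved to 80% power, the only slip is the missing inflation for loss (94 against 85), and the gap is 76% against 80%. A one-sided calculation would also explain the figure. Neither route rescues it: each drops a condition that the article states, and 76% falls short of both targets.

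The adequacy sentence most naturally describes the 214 target, not the 179, and it goes on to admit reduced sensitivity to smaller effects. This also stands. But the 214 target itself has about 76% power for 13 points and about 70% for the 12 points that the article derives from the minimal clinically important difference. The claim is unsupported even for the target.

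The recruitment shortfall is disclosed, and the Discussion concedes limited power against placebo. No number is attached, however, and the concession does not extend to the primary comparison. The 69% is the low end of a range that rests on an assumed split and loss. The noninferiority figures at margin 12 use the original calculation's zone; the analysis section sets 13, so the margin-13 figures are the ones to lead with. Covariate adjustment might raise power, but the sample-size calculation claims no such gain.

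Nothing in the article plans to read a null result as no relevant difference. That risk is a matter of interpretation, and how the results paper discusses such a result is a reporting choice.

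**Conclusion.** The point holds. The amended 85 per active arm does not reproduce from the article's stated conditions at 85% power (107 needed) or at 80% (94 needed). As amended, power for 13 points is about 76%. At 179 randomized it is about 69% with 10% loss and 74% with none. Noninferiority power at the 13-point margin is about 72% as amended and 64% at 179 with 10% loss, against the 77.6% stated for the original size.

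These figures assume SD 30, a 2:2:1 split of the 179 and the stated tests. The 85% benchmark is carried over from the original calculation, but the shortfall remains against 80%. Which condition was dropped to reach 85 cannot be told from the article.

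**What to change.** 1. The sponsor should state the power, sidedness, SD and loss used for the amendment and reconcile them with the two-sided 5% primary test. If the stated inputs stand, the paragraph should say that 85 per active arm with 10% loss gives about 76% power to detect 13 points (SD 30, two-sided 5%).
2. Add the position for the 179 randomized, using the actual split and loss once known. Until then: about 69–74% for the primary comparison, and about 64% for noninferiority at margin 13 with 10% loss (58% if the 12-point zone is meant). The difference detectable with 85% power is about 16 points with 10% loss.
3. Remove the statement that the adjusted size is sufficient, and the claim that the recalculation kept power adequate, or replace them with these figures.
4. As an optional addition, say that a nonsignificant primary result will be discussed through its 95% CI.

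The cost is wording in the analysis plan and the results paper. No test, margin, population or model changes, and no patients are added; the stated power becomes less favourable. The article reports that no analysis had been done by December 2024. If the correction is made before results are known, it cannot be seen as driven by them.

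### The amended size of 85 per arm does not follow from the stated inputs: with 10% loss it gives about 76% power for 13 points, and the original 85% would need about 107 per arm

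*Protocol article*

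**What the plan says.** All references are to the protocol article.

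- **Sample Size, original calculation.** The size of the toxin and baclofen arms "was calculated with the 2-sided test at a 5% significance level". The target is given as "For an 85% power and an FMA difference of 12 points between the" toxin and baclofen groups. The expected variation in FMA is put at 30 points, and the result is 120 per group, allowing for missing data and deviations without a stated percentage. The placebo calculation in the same section calls 30 points an SD.
- **Sample Size, amendment.** Recruitment was slow, so the target difference was raised to 13 points. As a consequence, the text says, "85 participants were required in both the" two main groups, "factoring in a 10% data loss". With 44 on placebo, the total is 214. No change of alpha, sidedness, SD or power is reported, and the power is not restated.
- **Statistical Methods for Primary and Secondary Outcomes.** The primary toxin-baclofen comparison is again two-sided at 5%.
- **Results.** Recruitment ended "with 179 randomized across 18 centers".
- **Strengths and Limitations.** The text reads "While the adjusted sample size is sufficient to detect clinically meaningful differences", and then concedes lower sensitivity to smaller effects. It describes the amendment as "recalculating the required sample size to maintain sufficient statistical power".

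**The concern.** Required sample size varies with the inverse square of the target difference. Moving from 12 to 13 points therefore multiplies the requirement by (12/13)² = 0.85, a cut of about 15%. The article goes from 120 to 85, a cut of 29%. A one-point change in the target cannot produce that if everything else is unchanged, and nothing else is reported as changed.

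What is at stake is how the primary result is read. The Abstract treats 13 points as a relevant effect, and the Discussion presents the amended size as adequate for clinically meaningful differences. If power at 13 points is well below what a reader would assume, a non-significant result could be taken as evidence against a relevant difference more readily than the design allows. The printed justification also cannot be reproduced.

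**Working it through.** **Inputs**

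- Two-sided 5% test: Sample Size, and again in Statistical Methods. z = 1.960.
- Power 85%: stated for the original calculation and carried over here as an assumption. z = 1.036.
- SD 30: an interpretation of the 30-point expected variation, supported by the placebo calculation.
- Target difference d: 12 points originally, 13 as amended.
- Loss 10%: stated for the amendment. Allocation between the two main arms is 1:1.

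**Formulas**

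n per arm = 2 (z_alpha + z_beta)² SD² / d². Enrolled = n / 0.9.
Power = Φ( d / (SD √(2/n)) − 1.960 ).
Results were also checked with the noncentral t distribution.

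**Step 1. Does SD 30 fit the article's own figures?**

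- Original primary size: 2 × 2.996² × 900 / 144 = 112.2, so 113 evaluable. Strictly, 10% loss would give 112.2 / 0.9 = 124.7, not 120. Read the other way, 120 less 10% leaves 108, with power 83.6% (83.3% by t). The fit is close but not exact.
- Placebo calculation: 60 less 10% is 54, against 108 on toxin, with margin 12 and one-sided 5%. The standard error is 30 √(1/54 + 1/108) = 5.0, and Φ(12/5.0 − 1.645) = 77.5%, against a printed 77.6%. This matches.

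SD 30 is therefore the best reading.

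**Step 2. What does 13 points require?**

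| Setting (SD 30, d = 13) | Evaluable per arm | Enrolled with 10% loss |
|---|---|---|
| Two-sided 5%, 85% power | 95.6 (96; 97 by t) | 106.3 to 107.8, about 107 |
| Two-sided 5%, 80% power | 83.6 (84; 85 by t) | 92.9 to 94.4, about 93 to 94 |
| Article | – | 85 |

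**Step 3. What does 85 per arm deliver?**

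85 × 0.9 = 76.5 evaluable. The standardized difference is 13 / (30 √(2/76.5)) = 2.680, and power is Φ(2.680 − 1.960) = 76.4% (75.9% by t). The type II risk is about 24%, or 1.6 times the original 15%. The difference detectable with 85% power is 30 √(2/76.5) × 2.996 = 14.5 points (14.6 by t).

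**Step 4. How could 85 arise?**

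- One-sided 5%, 85% power, SD 30: 76.6 / 0.9 = 85.1. This conflicts with the two-sided test.
- Two-sided 5%, 80% power, no loss allowance: 84 to 85. This conflicts with the 10% loss and lowers the power.
- Two-sided 5%, 85% power, 10% loss, SD about 26.8: 76.3 / 0.9 = 84.8. This conflicts with SD 30.
- Two-sided 5%, 80% power, 10% loss, SD about 28.7: 76.5 / 0.9 = 85.0. This conflicts with SD 30 and lowers the power.

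Each route departs from at least one stated input.

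**Step 5. Secondary note on the 179 randomized**

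Arm sizes are not given. At an assumed 2:2:1 split, 179 × 2/5 = 71.6 per main arm. Power at 13 points is 73.7% (73.1% by t) with no loss. With 10% lost and not recovered by imputation, 64.4 per arm remain and power is 69.1% (68.5% by t).

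**The case against.** The strongest reply is that the amended text gives no power figure. The 85% belongs to the 12-point calculation, and the article condenses a fuller protocol and amendment that may state another value. This stands as a caveat, but it does not rescue the number: at 80% power the stated inputs still need 93 to 94 per arm. The 30 points is also worded as an SD only for the placebo comparison, and the original 120 fits it only approximately. That too stands, and it is why the SD is listed as a reading.

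Three stronger readings are tempting and are not supported:

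- A reader might infer that the primary test was quietly made one-sided, because that route lands on 85.1. Two sections say two-sided, and other departures reach 85 equally well. The route actually taken is unknown.
- A reader might infer that the chance of missing the target effect roughly doubled. For the stated 85 per arm it is 24% against 15%. Something near twofold appears only after the recruitment shortfall is added, with an assumed split and, at the worst end, loss that imputation does not recover. The shortfall is openly reported and is not an arithmetic error. The adjusted size in the Discussion most naturally means the target of 214, not the 179.
- A reader might take the Discussion to assert that power was maintained. It states that as the aim of the recalculation, gives no figure, and admits reduced sensitivity to smaller effects. That admission is only partial, since sensitivity is already reduced at 13 points.

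It can also be said that enrolment closed in July 2020 and that correcting the figure changes neither test nor estimate. This is true, and it limits the remedy to wording. Covariate adjustment might add precision, but the sample-size text claims none and the first model is unadjusted.

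**Conclusion.** The concern holds in a limited form. The amended 85 per arm is not reproducible from the inputs the article states. With a two-sided 5% test, SD 30, a 13-point difference and 10% loss, it gives about 76% power. It falls about 22 per arm short of what the original 85% power requires, and 8 to 9 short at 80%.

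This rests on two assumptions: that 30 points is the SD, and, for the comparison with 85%, that the original power target carried over. The discrepancy remains under 80% power. The 68% to 74% range for the 179 randomized is a secondary note and depends on the assumed split and on how much loss imputation recovers.

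**What to change.** 1. In the amendment paragraph of Sample Size, state the alpha, sidedness, SD and power that produced 85. If the stated inputs stand, correct the claim: 85 per arm with 10% loss gives about 76% power for 13 points (two-sided 5%, SD 30), and 85% power would have needed about 107 per arm. If a different input was used, say which.
2. In Strengths and Limitations, qualify both the statement that the adjusted size suffices for clinically meaningful differences and the stated aim of keeping sufficient power, so that they agree with the corrected figure.
3. Optionally, note the approximate power for the 179 randomized, with the assumptions on arm split and loss spelled out.

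No further enrolment is proposed, and neither the primary test nor its alpha changes. The only cost is a less favourable stated power.
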